#### Sample size for DCEs

Johnson’s rule-of-thumb would lead to a sample of at least 75 participants regarding our DCE specifications (i.e., ten choice tasks per respondent, two alternatives, three levels per attribute as maximum) [27]. However, we aimed to double this number (i.e., at least 150 participants) following more advanced recommendations for statistical robustness [28, 29].

### Procedure

All participants (in the intervention and control groups) complete two QoL questionnaires (European Organisation for Research and Treatment of Cancer (EORTC) QLQ-C30 and QLQ-LC29 [30–32]) at the following time points: baseline (during the first 2 months of confirmed diagnosis of primary lung cancer) and 1, 2, 3, 4, 5, and 6 months after baseline (see. Figure 2). The first QoL measurement (baseline) takes place in the hospital by using a paper–pencil version of the QoL questionnaires for practical reasons. QoL data are entered manually into the online QoL monitoring system by a study coordinator at the study coordination unit so that patients and their CPs have online access to the results of the baseline QoL monitoring. All further QoL measures (1, 2, 3, 4, 5, and 6 months) will be completed on the patient`s mobile phone or computer via a secure web portal. For this purpose, after study entry each patient receives an email from the study coordination unit at the Tumor Center Regensburg with a link to activate the user account and assign a password. At 1, 2, 3, 4, 5, and 6 months after baseline each patient receives an email with a link to the QoL measurement, which is valid for two weeks. Patients who have not completed their QoL monitoring will receive two email reminders (after seven days and after 12 days). Once a QoL measurement has been completed it can no longer be edited. If participants have missed two QoL measurements in a row or if the QoL measurement at 6 months (primary endpoint) is missing they will be contacted by phone by one of the two study coordinators of the study coordination unit to check if there are any difficulties (e.g., use of the web application, internet access). If a participant has no regular access to the internet, there is also the possibility of a paper-based QoL measurement. For this purpose, QoL questionnaires are sent to the patient`s home by post at each timepoint for QoL measurement including a stamped return envelope.

**Fig. 2 Fig2:**
[figure not shown]
Schedule (SPIRIT diagram) of enrolment, interventions, and assessments

A user account is also created for each CP providing follow-up care of the study patients. Each CP has access to those study patients who have been assigned to his/her own practice.

Patients will be asked at 3 and 6 months after baseline and CPs at 6 months after baseline to complete an online questionnaire to evaluate their acceptance of the QoL monitoring system. All patients are treated according to the follow-up regimen of the German S3-guideline for lung cancer [33].

#### Intervention group

Patients in the intervention group receive, in addition to routine follow-up care [33], tailored QoL diagnosis and therapy for 6 months: After each QoL measurement, patients and their CPs have direct access to the results in the form of a QoL profile via a web application. In the case of an exclusively paper-based QoL measurement, patients receive their QoL profiles by post. The profile shows QoL on scales of 0–100 (worst to optimal QoL) comprising global QoL and seven different dimensions considering somatic (i.e., pain), psychological (i.e., emotional functioning), and social aspects (i.e., family life) (EORTC QLQ-C30 [30]). The QoL profile also takes into account specific discomfort that lung cancer patients suffer from (e.g., shortness of breath) (EORTC QLQ-LC29 [32]) (see Fig. 3). These dimensions were selected based on patient- and physician preferences that were determined in a preliminary study with DCEs as described above as well as on the results of two previous RCTs in breast cancer [6] and colorectal cancer patients [7]. A cut-off score < 50 points indicates a need for QoL therapy in each QoL dimension [6–9].

**Fig. 3 Fig3:**
[figure not shown]
Patients in the intervention group (quality of life (QoL) pathway) following recruitment for the randomised trial. This pathway is considered for routine clinical practice

CPs are regularly informed about their patients' QoL by automatically receiving information via email. They have access to their patients` QoL profiles as well as lists with professional healthcare providers so that specific complaints can be clarified at the next doctor-patient consultation and tailored therapies to improve QoL can be initiated.

For this purpose, the following therapeutic options for QoL improvement in patients with lung cancer have been defined based on previous studies of the complex intervention [6–8] and the expertise of the participating study clinicians:Pain therapyPsychotherapyPsycho-oncological careSocial supportNutritional counsellingPhysiotherapyFitness and sportsRespiratory therapyPalliative care

To provide continuous medical education, professional healthcare providers in this multi-professional network must meet in quality circles. As a result of the previous two RCTs (6; 7), regional network structures for QoL therapies have been established and are still available in the study region Upper Palatinate/Lower Bavaria. The Upper Franconia was added as a new study region to enhance the generalisability of the study results by implementing QoL monitoring in another region. CPs and patients obtain complete lists of the network of healthcare providers practicing in their region via the web portal or, if desired, by post to contact them easily for QoL therapy.

No recommendations are made regarding specific therapeutic options. The QoL profile provides a descriptive aid, but the decision of whether to initiate any specific QoL therapy is made by the CP and the patient. The QoL pathway of the patients in the intervention group is shown in Fig. 3.

#### Control group

In the control arm, QoL of patients is also assessed with the same QoL monitoring system used in the intervention group at study entry and at 1, 2, 3, 4, 5, and 6 months, but neither patients nor CPs have access to the results of their QoL measurements (no access to QoL profiles). However, complete lists of the network of local healthcare providers are also available for control group patients and their CPs via the web portal or if desired by post. Patients receive standard follow-up care according to the S3-guideline for lung cancer [33].

### Measures

#### Quality of life (patient)

QoL is measured by using the validated QoL questionnaires of the European Organisation for Research and Treatment of Cancer (EORTC), consisting of a core module (EORTC QLQ-C30 [30]) and a module for lung cancer patients (EORTC QLQ-LC29 [32]). The questionnaire is a self-administered instrument with a multidimensional structure measuring QoL on a four-point Likert scale or rather on a seven-point Likert scale for the global QoL dimension. Satisfactory internal consistency, good retest-reliability, and good construct and clinical validity have been demonstrated [30, 32]. For every dimension scores are uniformly transferred to a scale from 0 (= very bad QoL) to 100 (= very good QoL). A cut-off score < 50 points indicates a need for QoL therapy in each QoL dimension [6–9]. This decision criterion was chosen because the present study aims to highlight the patient’s perspective of subjective impairment. This is operationalised by dichotomising symptom scores with a majority of “quite a bit” and “very much” responses to the “bad” side of the spectrum (< 50) and “not at all” and “a little” responses to the “good” side (≥ 50). For outcome measurement, eight scales have been selected according to the results of both previous RCTs (9; 8) and our preliminary study examining patient and physician preferences: global QoL, shortness of breath, physical functioning, social functioning, fear of progression, emotional functioning, pain, and financial situation (Fig. 4).

**Fig. 4 Fig4:**
[figure not shown]
QoL profile of patients with lung cancer in the intervention group. The cutoff for a need for QoL therapy is < 50 points

#### Clinical cancer registry data

Based on the informed consent of the study patients and an approval from the Scientific Advisory Board of the Bavarian Cancer Registry, clinical cancer registry data from the Bavarian Cancer Registry will be linked with the QoL data (EORTC) of the study patients. Therefore, relevant study data are obtained directly from the registry preventing the collection of duplicate data (e.g. diagnostic information, therapy procedures). Details of the data linkage are described in the “ Data management and privacy” section.

#### QoL therapies

After 3 and 6 months, patients provide information about the QoL therapies they have used during the last 3 months via the web portal or, in the case of exclusively paper-based QoL measurements, per post.

#### Follow-up survey (evaluation of the QoL monitoring system)

Use of the QoL monitoring system [34]:Patients will be asked via the web portal or post at 3 and 6 months after baseline to answer questions relating to comprehensibility, user-friendliness, relevance, usefulness, patient-physician communication, and self-efficacy.CPs will be asked via the web portal at 6 months after baseline to answer questions related to patient-physician communication, future intention to use the QoL monitoring system and willingness to recommend it, and effects on quality of care.Acceptance of the QoL monitoring system [34]:For this purpose, an overview of possible acceptance models (e.g., the Unified Theory of Acceptance and Use of Technology (UTAUT) [35, 36]) is given by means of literature research and their applicability in our RCT is evaluated.Patients will be surveyed via the web portal or post 3 months after baseline.CPs will be surveyed via the web portal 6 months after baseline.

### Ethics and monitoring

This study received full ethical approval from the ethics committee of the University of Regensburg (internal reference number 23-3303_1-101). The trial is registered with ClinicalTrials.gov, trial registration number NCT06252233.

All adult patients with a new primary diagnosis of lung cancer can be included in the study (see exclusion criteria). The completion of QoL questionnaires (approximately 15 min) could be time-consuming for patients. It must also be considered that patient empowerment, as investigated in the intervention arm (patients have access to their QoL profiles), represents a risk for intervention group patients. However, an international RCT did not provide any evidence for the potential harm of patient empowerment by using a monitoring system [13]. Moreover, all study patients are under the continuous care of a CP who can react in the unlikely case of potential harm. Additionally, the CPs of the patients in the intervention group receive results of QoL measurements so that they can support them in cases of impaired QoL. The expected benefit is an improved detection of dimensions with reduced QoL in the intervention arm. It can also be assumed that control group patients will benefit from participating in the study, as their CPs will be sensitised to supportive, patient-oriented therapeutic options by having access to address lists of the multi-professional care network. The previously conducted RCTs on breast cancer patients [9] and colorectal cancer patients [8] did not show any evidence of possible harm elicited by the QoL pathway. In the long-term, this study is also important for improving QoL of individual oncological patients. There are no known risks for participating clinicians or CPs. The study is being conducted in compliance with ethical and scientific standards [37, 38]. We do not anticipate the need for provisions concerning post-trial care. If modifications of the study protocol (protocol version 2.5, September 16, 2024, are made (e.g., changes to eligibility criteria, outcomes, statistical analyses), all investigators will be informed, and changes will be made in ClinicalTrials.gov.

### Primary and secondary outcomes

Concerning primary objective 1, two endpoints will be analysed. The first endpoint is binary: Treatment is defined as successful (responder) if all eight dimensions of the QoL profile reach a value of ≥ 50 points 6 months after baseline (0 = very bad; 100 = very good). If the value of at least one QoL dimension is < 50 points, the treatment is considered unsuccessful (nonresponder), as substantial restrictions in even one QoL dimension can have a negative impact on a patient's overall QoL. As lung cancer is a serious disease with a short median survival time of approximately one year, QoL at 6 months after baseline was chosen as the timepoint to assess the primary endpoint [2, 39, 40]. We expect this period to be long enough to reveal significant effects of the investigated QoL intervention. The second endpoint, enhancing the credibility of the first primary endpoint, are the rates of patients with a QoL score ≥ 50 points separate for each dimension of the QoL profile 6 months after baseline. Both endpoints formulated above will be tested in strict order (1), (2); that is, a statistical testing procedure with a priori ordered hypotheses will be applied [41].

Concerning primary objective 2, QoL data will be supplemented with clinical cancer registry data to answer relevant medical and therapeutic questions. More research questions will be defined in two workshops using a nominal group technique with a group size of 7 to 15 participants (physicians, patients) [42].

Concerning secondary objectives 3–6, a variety of items concerning the perception of the QoL monitoring system will be analysed exploratively.

### Sample size

Trial sample size calculation is based on the first primary endpoint "responder", i.e. the relative frequency of patients with QoL scores in all eight dimensions ≥ 50 after 6 months (i.e. without a need for QoL therapy in the profile). This endpoint was used in RCTs on patients with breast cancer [9] and colorectal cancer [8]. As there is a lack of empirical evidence supporting this endpoint for patients with lung cancer, we are using the RCT protocol for patients with colorectal cancer as a guide. These patients are likely to have QoL deficits comparable to those of patients with lung cancer. We expect that 45% of patients in the intervention group will have no need for QoL therapy 6 months after treatment compared to 25% in the control group. With an α of 5%, 89 patients are needed in each group to detect the hypothesised difference with a targeted power of 80% (1-β) when using the Χ^2^-test of independence. To compensate for approximately 20% drop-outs (death, refusal) within the 6 month observation period, we will randomize 110 patients per group. Thus, the total sample size will be 220.

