## Background

### Background and rationale

Lung cancer is the leading cause of cancer mortality, accounting for approximately 1.80 million deaths worldwide in 2020 [1]. In Germany, in 2019/2020, lung cancer was the most common cause of cancer death in men (22%) and the second most common cause of cancer death in women (16%). In terms of the number of new cases, lung cancer was the second most common tumour location, with 35,890 new cases in German men, and the third most common tumour location in women, with 23,720 new cases. While the incidence rates for men have been declining since the 1990 s, they are increasing for women. In the majority of cases, patients are being diagnosed at an advanced stage [2].

The quality of life (QoL) of lung cancer patients is considerably impaired. Zabora et al. (2001) reported that the level of distress is highest in this patient group than in patients with 13 other common tumour diseases [3]. Over 90% of patients with advanced lung cancer suffer from fatigue, loss of appetite, shortness of breath, cough, and pain [4]. A systematic review investigating the QoL of patients with small cell lung cancer (SCLC) revealed a negatively impaired QoL in most domains compared to that of the general population with physical functioning being most affected [5]. In patients diagnosed with non-small cell lung cancer (NSCLC), Poghosyan et al. (2013) identified pain, dyspnea, coughing, and fatigue as the most common symptoms in the first few months after surgical resection [6]. Such unmet supportive care needs (e.g., physical, emotional, social, psychological, informational, spiritual, and practical needs) are associated with poorer QoL in patients with lung cancer [7].

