## Methods

### Trial design

The study is a two-armed, randomised, controlled, prospective, pragmatic, multicentre clinical trial with an intervention group and a control group. QoL of primary lung cancer patients will be assessed with an electronic patient- and physician-oriented QoL monitoring system at study entry and after 1, 2, 3, 4, 5, and 6 months of follow-up care. The subjects are randomly assigned (1:1 allocation ratio) to (1) an intervention group with tailored QoL diagnosis and therapy or (2) a control group with routine follow-up care. QoL data of each patient will be linked with clinical data from the Bavarian Cancer Registry for the purpose of data analysis. Thus, it is not necessary to collect patient-, tumour-, or treatment data exclusively for the purpose of this study, but rather existing data which already has been officially registered can be used. This saves a considerable amount of temporal and financial effort. This protocol is compliant with the SPIRIT 2013 reporting guidelines [21].

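### The 20% allowance for death plus refusal does not fit, under a constant hazard, the one-year median survival that the protocol cites; 110 per arm then gives about 75% power before any refusal, not 80%

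*Protocol article*

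**What the plan says.** The Sample size section plans on the first primary endpoint, the responder rate at 6 months, and assumes 25% responders under control and 45% under the intervention. The evaluable number is stated as follows: "With an α of 5%, 89 patients are needed in each group". It rests on a chi-square test and 80% power. That number is then raised to 110 per group, 220 in total: "To compensate for approximately 20% drop-outs (death, refusal"). One figure thus covers both causes of loss up to month 6, and the article gives no source for it.

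The Primary and secondary outcomes section explains why 6 months was chosen by describing lung cancer as a "serious disease with a short median survival time of approximately one year".

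The Statistical analyses section plans no imputation in the primary analysis. Counting patients with missing data as nonresponders is a sensitivity analysis only. The eligibility section sets no limit by tumour stage, upper age or type of therapy.

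**The concern.** The protocol uses the one-year median to choose the time point, but the sample-size paragraph does not appear to use it. If half the patients die within a year, a sizeable share will have died by month 6, and the 20% must cover them as well as refusals. A patient with no month-6 questionnaire cannot be classed as responder or nonresponder without imputation, so that patient leaves the chi-square test. If losses exceed 20%, fewer than the required patients are tested and the stated 80% power is not reached. A non-significant result would then be read against a power that the trial did not have.

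**Working it through.** **Inputs.** From the Sample size section: responder rates 25% and 45%, alpha 5% (taken as two-sided), power 80%, 110 randomised per arm, 20% loss. From Trial design: 1:1 allocation. From Primary and secondary outcomes: median survival about 12 months, endpoint at 6 months. Assumed here: equal loss in both arms, responder rates of 25% and 45% among those who reply, a constant hazard unless stated otherwise, and non-reply rates of 5%, 10% and 20% among survivors. The protocol gives no non-reply rate.

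**1. The plan's own figures.** With the pooled-variance formula, the mean rate is 0.35:

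n = [1.96·√(2·0.35·0.65) + 0.8416·√(0.25·0.75 + 0.45·0.55)]² / 0.20² = 88.09, so 89 per arm.

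This matches. Inflation gives 89/0.8 = 111.25, so 112. The stated 110 leaves 110 × 0.8 = 88 and power 80.0%. The difference is immaterial.

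**2. Deaths by 6 months.** With a constant hazard and a 12-month median, survival at 6 months is 0.5^(6/12) = 0.707, so 29.3% have died. Evaluable: 110 × 0.707 = 77.8 per arm.

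**3. Power at that number.** (0.20·√77.8 − 1.96·√0.455) / √0.435 = 0.67, which gives 74.9%. An exact calculation for the chi-square test at 78 per arm gives 75.9%.

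**4. Range over median survival and non-reply (constant hazard).** Entries in the last four columns are power at 110 randomised per arm.

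| Median (months) | Deaths by month 6 | No non-reply | 5% | 10% | 20% |
|---|---|---|---|---|---|
| 9 | 37.0% | 69.8% | 67.6% | 65.2% | 60.0% |
| 12 | 29.3% | 74.9% | 72.6% | 70.3% | 65.1% |
| 15 | 24.2% | 77.8% | 75.6% | 73.3% | 68.1% |
| 18 | 20.6% | 79.6% | 77.6% | 75.3% | 70.2% |
| 24 | 15.9% | 81.9% | 79.9% | 77.7% | 72.7% |

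**5. Range over hazard shape (12-month median).** Weibull survival at 6 months is 0.5^((6/12)^k).

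| Shape k | Deaths by month 6 | Power, no non-reply | Power, 10% non-reply |
|---|---|---|---|
| 0.8 | 32.8% | 72.6% | 68.0% |
| 1.0 | 29.3% | 74.9% | 70.3% |
| 1.2 | 26.0% | 76.7% | 72.2% |
| 1.5 | 21.7% | 79.1% | 74.7% |
| 2.0 | 15.9% | 81.9% | 77.7% |

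**6. What would make 20% right.** For deaths alone to equal 20%, the constant-hazard median must be 6·ln 2 / (−ln 0.8) = 18.6 months. At a 12-month median, the Weibull shape must be ln(ln 0.8 / ln 0.5) / ln 0.5 = 1.64. Either case leaves nothing for refusal.

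**7. Missing counted as nonresponder.** With all 110 per arm tested and both rates multiplied by 0.707, power is about 68%. This sensitivity analysis does not restore the 80%.

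**The case against.** A median fixes survival at one point only. The 29% rests on a constant hazard, and a rising hazard lowers it: shape 1.5 gives 79% power and shape 2 gives 82%, both with no refusal. This stands, and it is why the two passages are inconsistent under a stated assumption rather than in flat contradiction.

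The one-year figure describes the disease, not the trial cohort. Consent, exclusion of patients unable to complete the questionnaire, possible refusal by the coordinating practitioner, and entry up to 6 months after histology could all select longer survivors. This also stands, but the article gives no survival figure for such a cohort, and the median it does give is the one it uses for this endpoint.

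The non-reply rates are assumptions. The Procedure section provides two email reminders, a telephone call when the month-6 measurement is missing, and a postal route, all of which should keep non-reply down. Only the 75% for deaths alone is free of an assumed non-reply rate. The protocol does, however, itself list refusal as a cause of loss.

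Two stronger readings are tempting and not supported:

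- A reader might infer that the sample-size arithmetic is wrong. It is not: 89 and 110 both reproduce.
- A reader might infer that the 25% control rate is also too high, because the background reports that "the level of distress is highest in this patient group than in patients with 13 other common tumour diseases" while the sample-size section borrows from colorectal cancer ("These patients are likely to have QoL deficits comparable to those of patients with lung cancer"). Distress is not the proportion with all eight scales at 50 or above, and the protocol openly says that lung-cancer evidence is lacking. Even the direction of the effect depends on what is held fixed. At 89 per arm and control rates of 20% and 15%, power falls to 76% and 68% if the odds ratio stays at 2.45, but rises to 83.5% and 87.5% if the protocol's 20-point difference is kept.

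**Conclusion.** The point holds as an inconsistent planning input. Under a constant hazard and the protocol's own 12-month median, deaths alone (about 29%) exceed the 20% meant for death and refusal together. About 78 per arm remain evaluable and power is about 75%, or about 73% and 70% with an assumed 5% and 10% non-reply among survivors. The core shortfall is therefore modest, about five percentage points before non-reply.

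The 80% is reached if the hazard rises steeply (shape about 1.6 or more at a 12-month median) or the enrolled patients' median is about 18 to 19 months or more. At those thresholds there must be essentially no refusal; a 24-month median leaves room for about 5% non-reply (79.9%). The conclusion also assumes that patients without a month-6 value leave the primary test, which follows from the plan not to impute. The documents do not show that the trial will in fact miss 80%, because they give no survival figure for the enrolled cohort.

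**What to change.** In the Sample size section, replace the single 20% by two stated rates. The first is a 6-month death rate consistent with the cited survival, or a longer survival for the enrolled cohort with its justification. The second is a separate non-reply rate among survivors. Then restate the expected evaluable number per arm and the power: about 78 and about 75% before non-reply if the 12-month median and a constant hazard are kept. Add a short range over median survival, hazard shape and non-reply.

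This is a rewording of one paragraph. It needs no extra patients and leaves the design and analysis unchanged; the cost is a less favourable stated power. For scale only, regaining 89 evaluable per arm at 29.3% loss would take 89/0.707, that is 126 randomised per arm.
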